## Abstract

**Background:**

Due to the heterogeneous and systemic nature of the chronic obstructive pulmonary disease (COPD), the new guidelines are oriented toward individualized attention. Multidimensional scales could facilitate its proper clinical and prognostic assessment, but not all of them were validated in an international primary care cohort, different from the original ones used for model development. Therefore, our main aim is to assess the prognostic capacity of the ADO, BODEx and DOSE indices in primary care for predicting mortality in COPD patients and to validate the models obtained in subgroups of patients, classified by revised Global Initiative for Chronic Obstructive Lung Disease (2011) and updated Spanish Guideline (2014). Besides, we want to confirm that the prognostic capacity of all indices increases if the number of exacerbations is substituted by the interval between them and to assess the impact on health of the patient’s lifestyle, social network and adherence to treatment.

**Methods:**

Design: External validation of scales, open and prospective cohort study in primary care.

Setting: 36 health centres in 6 European high, medium and low income countries.

Subjects: 477 patients diagnosed with COPD, captured in clinical visit by their General Practitioner/Nurse.

Predictors: Detailed patient history, exacerbations, lung function test and questionnaires at baseline.

Outcomes: Exacerbations, all-cause mortality and specific mortality, within 5 years of recruitment.

Analysis: Multivariate logistic regression and Cox regression will be used. Possible non-linear effect of the indices will be studied by using Structured Additive Regression models with penalised splines. Subsequently, we will assess different aspects of the regression models: discrimination, calibration and diagnostic precision. Clinical variables modulated in primary care and the interval between exacerbations will be considered and incorporated into the analysis.

**Discussion:**

The Research Agenda for General Practice/Family Medicine highlights that the evidence on predictive values of prognostic indices in primary care is scarce. A prospective cohort like that of *PROEPOC/COPD* provides good opportunities for research into COPD and make communication easier between family practitioners, nursing staff, pneumologists and other professionals, supporting a multi-disciplinary approach to the treatment of these patients.

**Trial registration:**

ISRCTN52402811. Date: 15/01/2015. Prospectively registered.

**Electronic supplementary material:**

The online version of this article (doi:10.1186/s12890-016-0305-2) contains supplementary material, which is available to authorized users.

## Background

### Clinical and prognostic assessment of chronic obstructive pulmonary disease

Chronic Obstructive Pulmonary Disease (COPD) is a major public health problem, as there is considerable underdiagnosis and a high morbimortality. It is the fourth cause of death among males in European countries and its prevalence is expected to continue to increase [1]. Available epidemiological data show a wide variability in the incidence, prevalence and mortality in different countries [2]. In Spain, the EPI-SCAN study [3] found an overall prevalence for COPD of 10.2 % (CI 95 %: 9.2–11.1 %), higher among men than women (15.1 %/5.6 %), with 4.4 % (CI 95 %: 3.8–5.1 %) of cases classified as moderate to very severe (Stages II-IV of the Global Initiative for Chronic Obstructive Lung Disease [GOLD] classification).

COPD is characterized by a chronic poorly reversible airflow limitation, which is usually progressive if appropriate measures are not taken. Although the value for maximum forced expiratory volume in the first second (FEV1) has been the most commonly used prognostic variable, there is increasingly more evidence that FEV1 does not express the complexity and heterogeneity of COPD. Exercise tolerance, exacerbations, comorbidity, social support and quality of life are all dimensions that have been shown to be important predictors of mortality, each with its own strengths and limitations [4]. This has not led to abandoning the use of FEV1, with different cut-off thresholds to the classic ones, as a simple element with a high predictive value [5].

In its 2011 revised version, the GOLD [6] proposed a combined assessment of COPD based on the patient’s level of symptoms (measured on the modified Medical Research Council [MRC] dyspnoea scale or the COPD Assessment Test [CAT] questionnaire) and on the frequency of exacerbations in the last year or the degree of intensity of the obstruction (FEV1). This assessment has established the basis for drawing up guidelines for the individualized therapeutic management of COPD patients. Even though an advance, it caused controversy: depending on the criteria used for the classification, the allocation of patients could vary [7]; and the prognostic capacity of each group has also varied in different studies [8, 9].

In 2012, the *Guía Española de la EPOC (GesEPOC)* [the Spanish COPD guidelines, hereafter *GesEPOC*] became available [10]. These clinical practice guidelines classify COPD into 4 phenotypes: non-exacerbator, mixed COPD-asthma, exacerbator with emphysema and exacerbator with chronic bronchitis. It also links the phenotypes to the therapeutic activity, whether pharmacological or not, but there is still no quantitative evidence regarding the relationship between prognostic variables and each phenotype.

Therefore, the heterogeneous and systematic nature of COPD has meant that, in recent years, numerous variables are considered for its correct clinical and prognostic assessment. This has led to the construction of different multi-component or multi-dimensional scales. In a recent systematic review, 15 indices were analysed [11], most had a moderate to good prognostic value and some gave an appropriate assessment. The BODE index [12] (B = Body mass index; O = airflow Obstruction; D = Dyspnoea*;* and *E* = Exercise capacity, the 6-minute walk test [6MWT]) has been the most widely used, even though the inclusion of the 6MWT and the difficulty of incorporating this aspect for certain groups of patients limits its use in primary care settings.

For use in Primary Care (PC), the requirements for an index are [13]: a) it is simple to record and calculate; b) its components should be easy to record and register; c) its components should individually be clinically significant; d) it should be able to predict severity, with quality of life and mortality as outcomes; and e) it should predict future exacerbations and consumption of resources. With these criteria, the following indices could be selected for use in PC:The ADO (Age, Dyspnoea, Obstruction) index, derived from the BODE index in which age is included and with a higher predictive value than the original BODE; i.e., able to predict the probability of a specific patient dying in the next 3 years [14]. Recently, this scale has been recalibrated [15] in a very large cohort.The BODEx index, a simplified version of BODE in which the 6MWT is eliminated, substituting it with exacerbations without losing predictive capacity [16]. In the updated *GesEPOC* of 2014 [17], its use is proposed as a guide for referring patients and for selecting pharmacological treatment. This index is well known in Spain, but to date has had only limited use in the rest of Europe.The DOSE (Dyspnoea, Obstruction, Smoking, Exacerbation) index is the only one initially designed in PC, and although it first focused on health outcomes, its prognostic capacity has been demonstrated for mortality [18, 19].

The ADO and BODEx indices were designed for large cohorts in a hospital setting, in some cases with outpatients. To be applied in a different care setting, their validation is recommended, as has already been partially done in some studies [20, 21]. For the designers of each index, each one is applicable in primary care and each one has the best prognostic capacity. Comparing published studies, the BODEx [16] has an area under the curve (AUC) of 0.75, which has been exceeded by the modified ADO index [15] with an AUC of 0.80, while the value for the AUC for DOSE was not published [18].

COPD is a preventable and treatable disease, which requires a comprehensive approach in its assessment as well as multi-professional care. In addition to the indices described above, other aspects will be considered that are related to the health outcomes of the patient and to the preventative and/or therapeutic actions [22] usually managed by the patient and by primary care professionals. Such aspects have repeatedly shown that the quality of life of a patient can improve even without changes in functional parameters: a) Smoking and alcohol, with standardized tools in research and clinical practice for measurement and educational intervention. b) Physical exercise: The International Physical Activity Questionnaire (IPAQ) is the only one validated in Spanish and other languages, allowing international comparisons to be made. Nevertheless, there are other measurements that can be used, which have demonstrated the effect of exercise on health outcomes [23]. c) Social aspects, such as social network and family support [24]. d) Pharmacological follow-up: There is an electronic prescription-dispensing system within the electronic medical record (EMR) that allows an assessment of the follow-up of clinical guidelines and a comparison of the drugs prescribed and those collected from the pharmacy by the patient, as a measurement of adherence, essential for control of the disease by the patients themselves [25]. e) Comorbidities: Whether they have an underlying pathophysiological basis or are coincidental in time, comorbidities modulate and/or complicate the evolution of the diseases. Therefore, we will analyse the generic Charlson Comorbidity Index [26] and the specific COMorbidities in Chronic Obstructive Lung Disease (COMCOLD) index, which reflects the combined impact of five important comorbidities from the perspective of the patients and complements existing comorbidity indices that predict mortality [27].

The existence of the EMR makes it possible to incorporate in the follow-up three key aspects that are novel in prognostic studies: a) the interval of time between exacerbations (and not only their number); b) the existence of exacerbations treated in an emergency primary care setting (which could involve treatment of the acute phase, but maintains the medication prior to patient discharge, at present not counted as exacerbation); and c) assessment of adherence.

To sum up, the ADO and BODEx indices validated predominantly in cohorts from hospital settings can have a different prognostic capacity in a PC setting, due to the differences in severity and other clinical and social characteristics that depend on the setting in which patients are treated. Therefore, we need to verify if the capacity of these indices to discriminate and calibrate patients is maintained when they are applied in primary care.

Besides, the ADO, BODEx and DOSE indices, obtained in the PC setting, can show a different prognostic capacity in each subgroup, according to the GOLD classification and for each phenotype according to the *GesEPOC* classification. We expect that the prognostic capacity is better in groups C and D of the GOLD classification and in the exacerbator phenotypes of the *GesEPOC*, because these patients may be more widely represented in the population treated in the hospital and have lower intragroup variability. The prognostic capacity for the GOLD subgroups will vary according to whether CAT or MRC is used for their classification.

The aim of our study is to assess the prognostic capacity of the ADO, BODEx and DOSE indices in primary care, and to validate the models obtained in subgroups of patients, classified by the new combined assessment proposed in the revised GOLD methodology of 2011 and according to the phenotypes proposed in the updated *GesEPOC* of 2014. Besides, we want to confirm that the prognostic capacity of all indices increases if the number of exacerbations is substituted by the interval between them and to assess the impact on health of the patient’s lifestyle, social network and adherence to treatment.

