### Outcome variables

Survival (time to event) without exacerbation will be assessed during 5 years since patient recruitment. In addition, mortality (time to event) from all causes and those specifically due to respiratory causes will be analysed as health outcome at the end of the study. Data source will be EMR and death registry data if needed. Blind assessment of the outcome to be predicted is not feasible.

Exacerbations are defined as any sustained increase in respiratory symptoms (dyspnoea, cough and/or expectoration) that require modification of the usual treatment and/or hospital care -visit to the Emergency Room or admission- (for the BODEx index), as well as the exacerbations identified at the PC emergencies department (but without changing subsequent treatment). In this definition, admissions for pneumonia, pulmonary embolism and other causes of complications in COPD are not included.

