### Predictors

Assessment of predictors is done by GPs/nurses at baseline, without knowledge of the participant’s outcome, following the indices (ADO, BODEx, DOSE) definition. Formulas to calculate them are available in Additional file 1: Table S1.

They will be recorded in a specific database along with detailed patient history: date of birth, sex, height, weight, and body mass index. The spirometry test will be carried out according to protocol recommendations and the date of the first spirometric diagnosis of COPD will be recorded. Dyspnoea will be assessed according to the scale proposed by the British Medical Research Council for the ADO and BODEx indices. Associated diseases will be evaluated using the Charlson Comorbidity Index and COMCOLD, and the presence of other relevant illnesses, not included in Charlson, will be recorded, such as myopathy, osteoporosis, obstructive sleep apnoea-hypopnoea syndrome, and anxiety and depression disorders. The COPD Assessment Test (CAT) questionnaire will be used to assess the impact of COPD on the daily life and welfare of the patient, and its results will be used for categorisation according to the revised 2011 GOLD classification. Participating patients will be asked about tobacco consumption (packets/year), alcohol consumption (yes/no, units/week), physical exercise (Physical Activity Questionnaire short form (IPAQ), daily physical activity intense/moderate/low), current respiratory pharmacological treatment (in the stable phase), influenza and pneumococcal vaccine status, having received advice about their lifestyle and evaluation of the social support of the patient. The patient will be classified in accordance with the phenotypes defined by the *GesEPOC* [17].

The number of exacerbations in the previous years will be counted, in accordance with each index definition.

The ADO and modified ADO (from 0 to 14) indices, the BODEx index, DOSE index, Charlson index, COMCOLD index and the combined assessment of the GOLD score using the four possible models will be automatically calculated when introducing the variables that make up the computerised database.

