### Independent variables in the follow-up

The follow-up will be undertaken by clinical visits every 6 months. When the patient cannot make the appointment, follow-up will be by telephone interview or a review of the EMR. Information about the date of clinical exacerbations, admissions, visits to the emergency department (primary care or hospital) and mortality will be obtained by a review of the patient’s medical record, contact with the patient’s family and/or passive follow-up (from hospital and mortality records). Survival will be evaluated after 5 years. If cases are referred to a second care level, any specialist care appointments will be recorded.

Adverse events and dropouts during follow-up will be recorded, with the reason for them.

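### The objective of replacing the number of exacerbations by the interval between them sets a pre-baseline count against what reads as a follow-up variable, and it cannot apply to ADO

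*Protocol article*

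**What the plan says.** The aim at the end of the Background is to confirm that "the prognostic capacity of all indices increases if the number of exacerbations is substituted by the interval between them". The Abstract repeats it.

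- **Interval.** The Background lists it first among the items covered by "The existence of the EMR makes it possible to incorporate in the follow-up three key aspects that are novel in prognostic studies". The Abstract's analysis paragraph says it will be incorporated into the analysis.
- **Baseline record.** Under Predictors: "The number of exacerbations in the previous years will be counted, in accordance with each index definition". That section mentions no exacerbation dates and no interval.
- **Follow-up record.** The section headed "Independent variables in the follow-up" collects "Information about the date of clinical exacerbations, admissions, visits to the emergency department" and, in the same sentence, mortality.
- **Outcomes.** "Survival (time to event) without exacerbation will be assessed during 5 years since patient recruitment". All-cause and respiratory mortality are also analysed as time to event at the end of the study.
- **Models.** Data analysis plans logistic and Cox regression. It states no time window, landmark or time-updated coding for the interval.
- **ADO.** The Background defines it as "The ADO (Age, Dyspnoea, Obstruction) index".

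**The concern.** A comparison of two versions of one index is fair only if both are measured at the same moment, before the outcome starts to accrue. Here the number is fixed before recruitment, while the interval appears to come from the period in which deaths are counted. A patient who dies at one year cannot show an interval longer than one year. A patient who dies early is also less likely to have the two events that an interval needs. Either way the interval carries information about length of survival that has nothing to do with disease activity.

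The objective could then be confirmed when the interval has no prognostic value. A value known only after the visit also cannot serve an index meant for use at the visit. Separately, the phrase covering all indices conflicts with the article's own definition of ADO.

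**Working it through.** **Plan's own figures.** The plan gives no figure for this objective. Its sample size does not bear on the point, but it reproduces. The one-ROC formula is n(deaths) = [z(α/2)·√(0.0792(1+1/k)) + z(β)·√V]² / (AUC − 0.5)², with V = 0.0099·exp(−A²/2)·[(5A²+8) + (A²+8)/k] and A = 1.414·z(AUC). AUC 0.75, k = 8, two-sided 5% and power 90% give 14.76 deaths and 118.08 survivors. That is 132.8 per subgroup against the stated 133, and 3 × 132.8 × 1.20 = 478 against 477.

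**Inputs for the check.** From the protocol: N = 477, five years of follow-up, and 12.5% mortality at three years. At constant hazard the last gives 1 − 0.875^(5/3) = 20% at five years. Assumed, because the documents give no values: the exacerbation rates, their spread between patients, and 12.5% five-year mortality as the lower end.

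**Mechanism.** If m exacerbations fall at random over observed time T, the expected range is T(m−1)/(m+1), so the expected mean gap is T/(m+1). Take one exacerbation a year for everybody, unrelated to death.

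- A patient who dies at one year and had two events shows 1/3 = 0.33 years.
- A survivor with the expected five events shows 5/6 = 0.83 years.
- The chance of fewer than two events, and so no interval, is 2e⁻¹ = 74% for the patient observed one year and 6e⁻⁵ = 4% for the survivor.

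The first two lines make short intervals look lethal. The third works the other way if patients without an interval are scored as longest.

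**Interval alone against death, true AUC 0.50** (short interval taken as high risk; 0.5 to 1.5 a year; 12.5 to 20% dead at five years):

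- patients with at least two events only: 0.63 to 0.65
- all patients, fewer than two scored as longest: 0.34 to 0.46

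**Fitted models, still under the null.** N = 477, 300 runs per rate, gamma-distributed rates with means 0.8, 1.2 and 2.0 a year. Each logistic model holds the rest of the index plus either the baseline number or the interval. The rest of the index is assumed to give an AUC of about 0.73.

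| Handling of the interval | AUC, number | AUC, interval | Runs in which interval is higher |
|---|---|---|---|
| Fewer than two events set to own follow-up time | 0.73 | 0.744–0.768 | 93–99% |
| Fewer than two events set to five years | 0.73 | 0.755–0.759 | 96–98% |
| Only patients with at least two events | 0.73 | 0.747–0.757 | 83–86% |
| Two-year landmark | 0.72 | 0.72 | 50–52% |

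A fitted coefficient takes whichever sign suits the data, so an artefact in either direction raises the AUC. The planned bootstrap corrects overfitting, not this. In the landmark row the interval uses only events before year two, and only later deaths count; the comparison is then even.

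**Exacerbation-free survival.** No simulation is needed. An interval within follow-up requires two exacerbations, so every patient with a defined interval has already had the event.

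**ADO.** Age, dyspnoea and obstruction contain no exacerbation item. No substitution is possible.

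**The case against.** The strongest reply is that the premise is inferred. No sentence says the interval is computed from events after recruitment and entered as a fixed covariate. The Abstract lists exacerbations among predictors at baseline. Dates must be collected in follow-up anyway, because exacerbation-free survival is an outcome, and the heading about independent variables also covers mortality, so it is a poor guide to role. The six-week stability criterion means that some exacerbation timing is known at entry. Look-back windows, time-updated coding and values for patients with fewer than two events are normally left to an analysis plan, and Cox models can take time-updated covariates.

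Much of this stands. It rules out stating as fact that the plan uses a fixed post-baseline interval, and the silence on coding is not in itself a fault. What remains is what the article does say: it places the interval in follow-up, and for baseline it names only a count. An analyst who follows it would meet the problem.

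A reader might infer three further things that the documents do not support:

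- **That the bias always favours the interval.** For an unrefitted score it depends on coding and can reverse, as the 0.34 to 0.46 range shows.
- **That the substitution will be tested on exacerbation-free survival.** The main aim names mortality, and the substitution objective names no exacerbation outcome.
- **That adherence has the same fault.** The aim is to assess its impact on health, and nothing says it enters an index.

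**Conclusion.** The concern holds in a limited form. As described, the number is a pre-baseline count and the interval a follow-up variable, with mortality counted over the same period. If the interval is then entered as a fixed covariate, the comparison produces an association with death where none exists. In refitted models the interval had the higher AUC in 83 to 99% of null runs, against about half with a landmark. These sizes rest on assumed exacerbation rates and mortality; the direction for an unrefitted score also rests on how patients with fewer than two events are coded. If exacerbation-free survival is used as the outcome as well, the predictor is built from the outcome.

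The ADO point needs no assumption: the wording about all indices contradicts the article's own definition.

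Severity is moderate and confidence medium. A reader might take this as a threat to the study's main result. It is not: the objective is an added one, and validation of ADO, BODEx and DOSE from their original baseline items is untouched.

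**What to change.** 1. Define the interval from record dates before enrolment, over the same look-back window as the count. Fix in advance the value given to patients with no or one exacerbation, for example time since the last exacerbation, capped at the window length.
2. Use intervals from follow-up only as time-updated covariates in the Cox model, or after a fixed landmark with only later deaths counted. Label that analysis secondary.
3. Limit the substitution objective to BODEx and DOSE, and correct the wording in the Abstract and the aim.

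The cost is some rewording and one extra baseline field. The main drawback is that completeness of the look-back record may differ between countries. The landmark analysis also loses the deaths that occur before the landmark.

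### The interval between exacerbations is placed in follow-up and the number before baseline, so the planned comparison of the two as predictors of death is not interpretable as written

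*Protocol article*

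**What the plan says.** Five places in the protocol article bear on the point.

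- **Background, Clinical and prognostic assessment.** "The existence of the EMR makes it possible to incorporate in the follow-up three key aspects that are novel in prognostic studies". The first of these aspects is the interval between exacerbations. This is the only statement of where the interval comes from.
- **Independent variables in the follow-up.** Visits take place every 6 months. "Information about the date of clinical exacerbations, admissions, visits to the emergency department (primary care or hospital) and mortality will be obtained" from the medical record, the family or passive follow-up. These dates are what a follow-up interval would be built from.
- **Predictors.** "Assessment of predictors is done by GPs/nurses at baseline, without knowledge of the participant’s outcome". For exacerbations, this section mentions a count only: "The number of exacerbations in the previous years will be counted, in accordance with each index definition".
- **Background, aim.** "we want to confirm that the prognostic capacity of all indices increases if the number of exacerbations is substituted by the interval between them". The Abstract repeats this aim.
- **Design, Outcome variables and Data analysis.** Patients are followed for 5 years from recruitment, and all-cause and respiratory mortality are analysed as time to event. The models named are logistic regression and Cox proportional hazards. No landmark or time-dependent covariate is mentioned.

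The article gives no formal definition of the interval and no rule for patients with fewer than two exacerbations.

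**The concern.** On the plain reading, the two measures come from different windows. The number is fixed before the risk period starts. The interval accrues during it, alongside the deaths it is meant to predict. A patient who dies at 1 year can only show gaps shorter than 1 year, while a survivor can show gaps of almost 5 years. Interval length then carries information about survival time whether or not exacerbations affect mortality.

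The stated aim to confirm a gain from substituting the interval for the number is at stake. A difference in AUC between the two versions of an index would mix any true prognostic difference with this truncation effect, and the reader could not separate them. A score built on later exacerbations also could not be computed at the baseline visit, where a primary care index would be used.

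**Working it through.** The article states no figure for the interval-versus-number comparison, so there is none to reproduce. The check asks what the comparison would show if exacerbations had no relation to death.

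**Inputs from the article**
- 3-year mortality 12.5 % (Sample size)
- N = 477 (Sample size)
- Follow-up 5 years (Design)

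**Assumed, because the article gives no value**
- Constant death hazard
- Poisson exacerbations at a mean of 0.6 to 2.0 per patient-year with gamma variation between patients (a second set used 0.5, 1 and 2 per year, with and without such variation)
- Exacerbation rate independent of death

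**Mortality**
- Hazard: −ln(1 − 0.125)/3 = 0.0445 per year.
- 5-year mortality: 1 − exp(−5 × 0.0445) = 0.200, about 95 deaths in 477.
- 2-year mortality: 1 − exp(−2 × 0.0445) = 0.085.

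**Follow-up interval as a fixed covariate.** The true AUC is 0.50. A shorter interval is scored as higher risk of death within 5 years.

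| Measure | Mean rates per year | AUC under the null |
|---|---|---|
| Mean follow-up gap, patients with ≥ 2 exacerbations | 0.6–2.0 | 0.63–0.65 |
| Number before baseline, same patients | 0.6–2.0 | 0.52–0.54 |
| Number before baseline, all patients | 0.5–2 | 0.50 |
| Gap; patients with < 2 given their own follow-up time | 0.5–2 | 0.57–0.69 |
| Follow-up time divided by number | 0.5–2 | 0.54–0.73 |
| Gap; patients with < 2 given 5 years | 0.6–2.0 | 0.39–0.45 |

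In the second row the number departs slightly from 0.50 because requiring two follow-up exacerbations is itself a selection: those who die early yet qualify tend to have high rates. In the last row the direction reverses because patients who die early have had less time for two exacerbations, so they more often receive the long value.

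In a Cox model at N = 477 (rates 0.5 to 2, gamma variation), the mean gap in patients with at least two exacerbations is falsely significant in 49 to 68 % of replicates at a nominal 5 %. The baseline number is so in 4 to 5 %.

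**Window closed before the risk period**
- Interval from an assumed 2-year look-back before baseline: AUC 0.50, Cox rejection 4 to 7 %.
- Landmark at 1 or at 2 years, among patients still alive: AUC 0.50.

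**At index level.** The aim concerns whole indices. An illustrative null simulation assumed other components worth 0 to 7 points with an AUC of about 0.77, and an exacerbation item worth 0 to 2 points. Among patients with at least two follow-up exacerbations, the false gain averaged 0.024. In the whole cohort, with patients under two given zero points, the interval version was worse by 0.05 to 0.06. The cut-offs are assumptions, but size and sign again depend on the scoring.

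**The case against.** The strongest reply is that the article never defines the interval. The Abstract and the Predictors section describe predictors as baseline measures, and substituting the interval for the number could mean the same past exacerbations expressed differently. The follow-up section lists mortality beside exacerbation dates, so its heading does not prove that the dates are predictors. Those dates are needed in any case for the exacerbation outcome. The article is condensed, and an analysis plan that is not shown could specify a landmark or a time-dependent covariate.

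Part of this stands: a pre-baseline interval is not ruled out. But the one sentence that locates the interval puts it in follow-up, and no passage mentions baseline dates or a baseline interval. This is therefore more than missing detail, because following the text gives a biased comparison. If only a count is recorded at baseline, an analysis plan cannot create pre-baseline gaps without going back to the record.

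Two stronger readings are tempting, and the documents do not support them.

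- A reader might infer that the interval is bound to look better, so that the aim is answered yes in advance. The reversed coding shows otherwise, and large differences between a bare interval and a bare count do not carry over to whole indices.
- A reader might infer that follow-up intervals will predict exacerbation-free survival, where a gap would exist only after the outcome had happened. The Outcome variables section does plan that outcome ("Survival (time to event) without exacerbation will be assessed during 5 years since patient recruitment"), but no passage uses the interval to predict it.

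**Conclusion.** The point holds in a limited form. As written, number and interval come from different windows, and the interval's window overlaps the period in which deaths are counted. A follow-up interval entered as a fixed covariate can look clearly prognostic when exacerbations are unrelated to death (AUC about 0.63 to 0.65 in patients with at least two follow-up exacerbations). With another coding of the remaining patients it looks worse than chance (0.39 to 0.45). The comparison cannot be interpreted in either direction.

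These figures rest on the plain reading that the interval is a follow-up measure, on fixed-covariate analysis, and on assumed rates of 0.6 to 2.0 per year. The distortion of a whole index would be smaller than that of the bare interval and depends on the scoring. The affected aim is an additional one; the main validation of ADO, BODEx and DOSE with baseline scores does not depend on it.

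**What to change.** State in the Background, Predictors and Data analysis sections that number and interval are derived from the same exacerbations in the same window, and that this window closes before the risk period starts.

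- **Preferred:** extract from the electronic record the dates of the pre-baseline exacerbations already counted, and use those intervals only. The cost is some extra date extraction. Recruitment began in February 2015, so it would be retrospective for patients already enrolled.
- **Otherwise:** use a landmark analysis with both measures taken from the landmark window and only later deaths counted, or treat exacerbation history as a time-dependent covariate that uses only information up to each time point.

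A 24-month landmark is a fallback only. At the planning rate it drops about 8.5 % of patients, and 0.085/0.200 is about 43 % of the 5-year deaths.

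Whichever route is taken, define the interval and fix in advance how patients with fewer than two exacerbations in the window are scored.
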